### Serious adverse events (SAE)

All events which meet the definition of serious will be collected and recorded in the participant notes and the Case Report Form (CRF). SAEs will, in addition, be reported to the trials office immediately and within 24 h of the principal investigator being made aware of the event. Allergic reaction to chlorohexidine requiring treatment will be considered a serious adverse advent.

Events not considered an SAE in PREPS include:Hospitalisation for delivery of the babyThe development of infection and sepsis in the post-natal period that requires inpatient treatment or prolongation of hospitalisation as this is an outcome of the trialObstetric haemorrhageDamage to bowel or bladder during surgeryProlonged hospitalisation due to neonatal complicationsThromboembolic events

All other events not detailed above that meet the definition of a SAE should be reported as detailed below.

SAEs should be reported on an SAE Form. When completing the form, the PI will be asked to define the causality and the severity of the SAE. Causality will be assessed as definitely related, probably related, possibly related, unlikely to be related or unrelated. On becoming aware that a woman has experienced an SAE, the Investigator *or delegate(s)* should report the SAE to their own Trust in accordance with local practice and to the BCTU trials office. On receipt of an SAE form, the Chief Investigator (CI) or delegate(s) will independently determine the seriousness and causality of the SAE. An SAE judged by the PI or CI or delegate(s) to have a reasonable causal relationship with the intervention will be regarded as a related SAE. The causality assessment given by the PI will not be downgraded by the CI or delegate(s). If the CI or delegate(s) disagrees with the PI’s causality assessment, the opinion of both parties will be documented, and where the event requires further reporting, the opinion will be provided with the report. The CI *“or delegate(s)”* will also assess all related SAEs for expectedness. If the event is unexpected (i.e. is not defined in the protocol as an expected event), it will be classified as an unexpected and related SAE. BCTU will report all events categorised as unexpected and related SAEs to the main Research Ethics Committee (REC) within 15 days. The main REC and sponsor will be notified immediately if a significant safety issue is identified during the course of the trial.

## Sample size and data analysis

### Sample size

Since this is a feasibility study, no formal sample size calculations have been undertaken. The feasibility study is not designed or powered to detect a statistically significant difference in efficacy between the two treatment arms. A total sample size of 250 participants would agree with existing literature which suggests that the size of the feasibility study should be at least 10% of the anticipated size of the substantive study [12]. A recruitment target of 250 participants has been chosen for this feasibility study as we expect this number will be sufficient to provide estimates of the feasibility outcomes.

Preliminary sample size calculations were computed for the full RCT. Vaginal cleansing with povidone iodine has been evaluated in a Cochrane review which comprised of seven trials randomising 2816 women (2635 analysed) estimating the effects of vaginal cleansing (povidone-iodine) on post-caesarean infectious morbidity. The risk of bias was generally low, with the quality of most of the studies being high. Vaginal preparation immediately before caesarean delivery significantly reduced the incidence of post-caesarean endometritis from 8.3% in control groups to 4.3% in vaginal cleansing groups. To detect a difference of this size with 90% power and alpha at 5%, we would require 1548 participants. In addition, to account for an anticipated 10% loss to follow-up, we would need a total of 1720 participants.

### Analysis of outcome measures

A separate statistical analysis plan for the PREPS feasibility study will provide a detailed description of the planned statistical analyses. A brief outline of the planned analyses is given below.

All *clinical* outcomes will be analysed according to the treatment arm to which they were randomised (i.e. vaginal cleansing or no cleansing) irrespective of compliance with the randomised treatment allocation, as per the intention to treat principle. Women who did not undergo a CS will be excluded from the analyses.

All *feasibility* outcomes will be analysed pooling the two randomised groups and presenting overall estimates of proportions with 95% confidence intervals, as well as estimates by centre.

All outcomes will primarily take the form of simple descriptive statistics (e.g. proportions and percentages, means and standard deviations) and where appropriate, point estimates of effect sizes (e.g. mean differences and relative risks) and associated 95% confidence intervals.

### Decision to continue to a definitive trial

The decision to continue to a full trial will be decided by pre-defined stop-go criteria. A traffic light system has been designed that will determine progression.

#### Stop-go criteria

Recruitment rates: the proportion of women randomised into the trial of the 250 recruitment target.Adherence to the allocated intervention: the proportion of women who received their allocated intervention out of all those randomised.Successful completion of follow-up: the proportion of women remaining in the trial (i.e. not withdrawn as per criteria below) who successfully complete the planned follow-up process for both the 14- and 30-day telephone interview.Study drop-out: withdrawal from the study.

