## Outcomes

All feasibility outcomes will be assessed overall and by centre. Recruitment will take place for a minimum of 12 weeks and a maximum of 20 weeks, across the four maternity sites.

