#### Traffic light system

Green light: recruitment rate > 90%, adherence rate > 75%, follow-up rate > 90% and dropout rate < 15%. If all four criteria are met, we will proceed to a full trial with the protocol unchanged (unless there is a clear message from the focus groups that would improve the protocol).

Amber light: recruitment rate 80–90%, adherence rate 50–75%, follow-up rate 75–90% or dropout rate 15–30%. If one or more of our amber light criteria are met, we will plan to adapt the protocol in light of the feedback from the focus groups and our experience to improve whichever criteria are not at the ‘green-light’ level before proceeding to full trial. We will assess whether adaption of the protocol will require a further feasibility study or pilot study before progressing.

Red light: recruitment rate < 80%, adherence rate < 50%, follow-up rate < 75% or dropout rate > 30%.

If one or more of these criteria are met, we would consider the current protocol not feasible and not progress to a full RCT.

The Trial Oversight Committee will take into consideration statistical uncertainty around these rates using 95% confidence intervals.

Missing data: Every attempt will be made to collect full follow-up data on all study participants; it is thus anticipated that missing data will be minimal and the strategies needed to achieve this are part of this feasibility RCT. The main analysis will use available data only; however, the amount of missing data will be assessed, and if necessary, sensitivity analyses will be undertaken.

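### The recruitment stop-go criterion is not tied to a recruitment window, and the proportion-type 95% confidence interval described for it is too narrow

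*Protocol article*

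**What the plan says.** Protocol article, Stop-go criteria (under Decision to continue to a definitive trial): the recruitment rate is "the proportion of women randomised into the trial of the 250 recruitment target". The Stop-go criteria list under Outcomes gives the same definition.

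Protocol article, Outcomes: "Recruitment will take place for a minimum of 12 weeks and a maximum of 20 weeks, across the four maternity sites".

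Protocol article, Traffic light system: recruitment is green above 90%, amber from 80% to 90% and red below 80%. Any one red criterion means that the trial does not progress. The Trial Oversight Committee is to consider "statistical uncertainty around these rates using 95% confidence intervals", and recruitment is not excepted.

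Protocol article, Analysis of outcome measures: feasibility outcomes are pooled over the arms and given as proportions with 95% confidence intervals, overall, with estimates by centre. The section calls itself a brief outline and leaves detail to a separate analysis plan.

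Protocol article, Other feasibility outcomes: the list includes the share of eligible women who were approached, and women randomised with verbal consent out of those having an emergency caesarean. It does not list women randomised out of all eligible or all approached women.

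**The concern.** Two features of the criterion do not fit together.

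First, the denominator of 250 carries no time. The window may differ by a factor of 20/12 = 1.67, and nothing says that recruitment runs to 20 weeks if 250 has not been reached. A shortfall could therefore mean slow recruitment or a short window, and the criterion does not separate the two.

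Second, a confidence interval for a proportion treats the denominator as a set of sampled women, each of whom was or was not recruited. The 250 are a planning number. What varies by chance is the count of women who arrive and are randomised in a given time. An interval for x/250 as a proportion shrinks towards zero width as the count nears target and has no value above 100%, although neither is a property of the recruitment process.

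Recruitment alone can stop progression, and the committee is told to use the interval in that decision.

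**Working it through.** **Inputs.** Target 250; thresholds 90% and 80%; window 12 to 20 weeks; four sites (Outcomes, Stop-go criteria, Traffic light system). The 250 has no formal sample size calculation behind it, so there is no derived figure to reproduce for the target itself. Constant weekly speeds are my assumption, shown as a range.

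**Thresholds as counts.** 0.90 × 250 = 225 and 0.80 × 250 = 200. Green is 226 women or more, amber 200 to 225, red 199 or fewer.

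**Colour by window length.** Expected count = speed × weeks. Probabilities are Poisson with that mean.

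| Speed (women/week) | Weeks | Expected count | Share of 250 | P(red) | P(amber) | P(green) |
|---|---|---|---|---|---|---|
| 12.5 | 12 | 150 | 60% | >0.999 | <0.001 | <0.001 |
| 12.5 | 16 | 200 | 80% | 0.49 | 0.47 | 0.04 |
| 12.5 | 20 | 250 | 100% | <0.001 | 0.06 | 0.94 |
| 15 | 12 | 180 | 72% | 0.93 | 0.07 | <0.001 |
| 15 | 16 | 240 | 96% | 0.004 | 0.17 | 0.83 |
| 15 | 20 | 300 (target passed) | 120% | <0.001 | <0.001 | >0.999 |

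At one underlying speed, the expected result goes from red to green within the permitted window.

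**What the cap does fix.** A green result needs at least 226 women in at most 20 weeks, so it implies at least 226/20 = 11.3 women per week over the four sites.

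**Interval at the lowest green count, 226/250 = 90.4%.**

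- As a proportion (Clopper-Pearson): 86.1% to 93.8%, width 7.7 percentage points.
- As a count (exact Poisson): 197.5 to 257.5 women. Divided by 250, this is 79.0% to 103.0%, width 24.0 points.
- Ratio of widths: 24.0/7.7 = 3.1.

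The large-sample formulas show why. The proportion standard error is √(0.904 × 0.096/250) = 1.86 points. The Poisson one is √226/250 = 6.01 points. The ratio is 1/√(1 − 0.904) = 3.2.

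**At the lowest amber count, 200/250 = 80%.** Proportion interval 74.5% to 84.8% (10.3 points); Poisson 69.3% to 91.9% (22.6 points); ratio 2.2.

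**At 250/250.** Proportion interval 98.5% to 100%; Poisson 88.0% to 113.2%.

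So at 226 the proportion interval covers amber and green only, while the count interval just reaches red.

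**A time-based version.** The expectation over 20 weeks is 250/(4 × 20) = 3.125 women per site per open week. With all four sites open for 20 weeks, 226 women gives 226/80 = 2.825, and 2.825/3.125 = 90.4%, identical to the present measure. With 150 women in 12 weeks, 150/48 = 3.125, which is 100% (green), against 60% (red) as written. The two versions part company when recruitment ends early and short of target, or when sites open at different times.

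**The case against.** A share of a recruitment target is a common feasibility criterion. The 12-to-20-week sentence can also be read to mean that recruitment closes early only once 250 is reached and otherwise runs to the cap. On that reading every shortfall is a 20-week count and converts directly to a speed. This is a sensible reading, but the article does not state it, and stating it is one of the two remedies below.

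The article never names a binomial interval, and the unseen analysis plan may give the method. That is fair as far as it goes. Still, the article itself describes the feasibility outcomes as proportions with confidence intervals and applies intervals to all four traffic-light rates. Followed as written, that gives the narrow interval for recruitment.

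On uptake, the article already lists an emergency-caesarean measure and needs counts of eligible and approached women. The gap is an unlisted ratio, not an absence of uptake data.

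A reader might also infer three stronger things that the document does not support:

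- That the criterion says nothing about speed. The 20-week cap gives green a floor of 11.3 women per week.
- That any confidence interval here is meaningless. A Poisson interval for the count, or for women per site-week, is well defined.
- That the criterion passes a speed too slow for the full trial of 1720 women. The article gives neither a duration nor a number of sites for that trial, and projecting from four sites would assume what it does not say. Nor does 226 women in 12 weeks against 226 in 20 weeks show a wrong decision: both are green now, and both stay green on the time-based version (151% and 90.4% of 3.125).

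**Conclusion.** The concern holds in a limited form. The recruitment criterion lacks a time base. Should recruitment close early and short of 250, its colour can run from red to green at the same underlying speed (60%, 80% and 100% of target at 12, 16 and 20 weeks for 12.5 women per week). The proportion-type interval described for it understates the uncertainty by a factor of about 3 at the green boundary and about 2 at the lower amber boundary.

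The window result assumes a constant weekly speed and matters only if closure short of target before 20 weeks is possible, which the text leaves open. The interval result assumes Poisson arrivals over a fixed window; if weekly recruitment varies more than that, the proper interval is wider still. The thresholds themselves, the target of 250 and the full-trial sample size are not called into question.

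**What to change.** Keep the 90% and 80% thresholds and tie them to a stated time base, in one of two ways:

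- state that recruitment runs the full 20 weeks unless 250 is reached earlier, and that the criterion is judged on that basis; or
- define the criterion as women randomised per site per open week, judged against 250/(4 × 20) = 3.125.

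State that the 95% confidence interval for the recruitment criterion is a Poisson interval. Leave the intervals for adherence, follow-up and drop-out as proportions, since those have women as denominators.

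Report randomised/eligible and randomised/approached with binomial 95% intervals as supporting uptake measures, outside the traffic light.

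The cost is a few sentences, plus randomisation dates, site opening dates and the screening counts already needed for the other feasibility outcomes. No additional women are needed. The downside is a wider, less favourable interval around the recruitment figure. The Trial status section says that recruitment had already opened, so the change should be documented before the progression decision is taken.

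### The adherence stop-go rate pools both arms, and controls adhere by default, so green needs only about half of the cleansing arm to be cleansed and red can hardly ever fire

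*Protocol article*

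**What the plan says.** Under Decision to continue to a definitive trial, Stop-go criteria, adherence is "the proportion of women who received their allocated intervention out of all those randomised". The list of stop-go outcomes in the Outcomes section uses the same denominator. Analysis of outcome measures says that feasibility "outcomes will be analysed pooling the two randomised groups and presenting overall estimates of proportions with 95% confidence intervals", with estimates by centre as well. No adherence estimate or threshold is given by arm.

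The Traffic light system sets the bands, in per cent: green at "adherence rate > 75", amber at "adherence rate 50–75" and red at "adherence rate < 50". If all four criteria are green, the full trial goes ahead without altering the protocol, unless the focus groups point clearly to an improvement. Any amber criterion means adapting the protocol first and considering a further feasibility or pilot study. Any red criterion means no full trial. The oversight committee is to take 95% confidence intervals into account, but no rule for doing so is given.

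**The concern.** The two allocations are not equally hard to deliver. A woman allocated to cleansing adheres only if someone in theatre does it. A woman allocated to control adheres if nothing departs from usual care. Justification for intervention says vaginal cleansing has not been taken up in obstetric practice, so near-complete control adherence is the natural expectation. Averaging the arms then mixes the quantity of interest with one that is close to 100% by construction.

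Adherence is the only one of the four stop-go criteria that bears on whether cleansing can be delivered, and the Aims include finding out whether the intervention can be carried out in a multi-centre trial. If the rate is half automatic, the cut-offs of 75% and 50% do not mean what they appear to mean. The study could report green, and start the full trial unchanged, with nearly half of the cleansing arm uncleansed.

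**Working it through.** **Inputs.** 250 women, 125 per arm (Abstract); 1:1 allocation and a control of no cleansing (Feasibility study design; Randomisation); the bands above (Traffic light system); 8.3% versus 4.3%, 90% power, alpha 5%, 1548 women, 1720 after 10% loss (Sample size). Control adherence is not stated. I take 100% as the base case and 90% to 100% as the range.

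**The plan's own figure.** The adherence bands come with no derivation, so the only figure to reproduce is the full-trial size. For two proportions with pooled variance under the null, two-sided alpha 5% and no continuity correction:

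n per arm = [1.960 × √(2 × 0.063 × 0.937) + 1.282 × √(0.083 × 0.917 + 0.043 × 0.957)]² / 0.04² = 774 after rounding up.

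The total is 1548, and 1548 / 0.9 = 1720. Both match the protocol.

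**What the thresholds require.** Let t be adherence in the cleansing arm and c adherence in the control arm. With equal arms the pooled rate is A = (t + c)/2, so t = 2A − c. Green (A > 0.75) means t > 1.5 − c. Red (A < 0.50) means t < 1 − c.

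| Control adherence c | Green needs t above | Red needs t below |
|---|---|---|
| 100% | 50% | 0% (impossible) |
| 98% | 52% | 2% |
| 95% | 55% | 5% |
| 90% | 60% | 10% |

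In counts, green needs at least 188/250. If all 125 controls adhere, that is 188 − 125 = 63 of 125 cleansed, or 50.4%. With none cleansed the rate is 125/250 = 50.0%, which is amber.

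**How often each light would show.** Exact probabilities from the sum of two binomials, 125 women each:

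| True t | Light | c = 100% | 98% | 95% | 90% |
|---|---|---|---|---|---|
| 60% | green | 0.99 | 0.96 | 0.85 | 0.50 |
| 50% | green | 0.50 | 0.33 | 0.15 | 0.03 |
| 20% | red | 0 | <0.0001 | 0.0001 | 0.010 |
| 10% | red | 0 | 0.001 | 0.05 | 0.46 |
| 0% | red | 0 | 0.92 | 0.998 | 1.00 |

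With four women in five uncleansed, red has at most a 1% chance anywhere in this range.

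**Effect on the full trial.** Assume that uncleansed women carry the control risk and that 8.3% versus 4.3% is the effect of cleansing actually received. The cleansing-arm rate is then 8.3% − t × 4.0 percentage points.

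- At t = 50.4%, the lowest green result with full control adherence, the contrast is 8.3% versus 6.28%. Power with 774 per arm is 33.2%.
- At t = 50%, the contrast is 8.3% versus 6.3% and power is 32.7%. Restoring 90% power would need 7108 women analysed, or 7898 with 10% loss.
- At t = 100%, power is 90.0%, as planned.

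**The same bands on the cleansing arm alone.** Green would need at least 94/125 (75.2%), and red would fire at 62/125 (49.6%) or fewer.

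**The case against.** *Control adherence may not be 100%.* This is fair. The Intervention section says these doctors know vaginal cleansing from gynaecological surgery, so some controls may be cleansed. Red is strictly impossible only at exactly 100%. With even 2% contamination, a complete absence of cleansing would usually show red. But contamination raises the green cut-off only to 60% at c = 90%, and red still needs fewer than one woman in ten cleansed. It also makes the pooled rate harder to read, because poor delivery and contamination lower it alike.

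*Some women may be non-adherent in both arms.* The exclusion of women who had no caesarean stands in the paragraph on clinical outcomes, so it is not certain that it covers adherence. If, purely for illustration, 10% of both arms counted as non-adherent for such a reason, A = 0.9(1 + t)/2. Green then needs t > 67% and red t < 11%. The bar moves for reasons unrelated to delivery, and red stays remote.

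*Amber still protects.* Zero cleansing gives amber at best, and amber obliges the team to adapt the protocol. So total failure could not lead straight to an unchanged full trial. The real exposure is a false green with roughly 50% to 65% cleansed.

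*The committee looks at confidence intervals.* If green required the lower 95% limit to exceed 75%, it would need 201/250 (Wilson) or 202/250 (Clopper-Pearson). With full control adherence that is 76 or 77 of 125 cleansed, about 61% to 62%. This would help but not cure, and no such rule is written. Requiring the upper limit to lie below 50% would make red harder still.

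*The full-trial size is only preliminary.* This is true, and the study is meant to inform it. The 33% therefore describes what follows if 1548 is kept; it is not a forecast. Yet a pooled rate just above 75% gives no signal that the size needs revisiting.

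*Recruitment and follow-up are the main questions.* The Discussion does say so. That bears on priority. It does not make the adherence rule work.

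**Conclusion.** The criterion is wrong as written. The pooling is explicit in both the denominator and the analysis section, so an unseen analysis plan that also described adherence by arm would leave the published decision rule unchanged. The by-centre estimates do not help, because they pool the arms too.

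The one substantive assumption is high control adherence. Over 90% to 100%, green tolerates about 40% to 50% of the cleansing arm going uncleansed, and red requires almost no cleansing at all. The phrase about half is the limiting case at full control adherence; that red can hardly ever fire holds across the range. The power loss depends further on the two dilution assumptions and on keeping 1548 women.

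**What to change.** Define the stop-go adherence rate on the cleansing arm: women allocated to cleansing and recorded as having received chlorhexidine cleansing, divided by all women allocated to cleansing. Report the proportion of controls who were cleansed as a separate contamination rate. Exempt adherence from the pooling sentence in Analysis of outcome measures. State whether women who had no caesarean stay in the denominator.

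The existing bands can be carried over, with green at 94/125 or more and red at 62/125 or fewer. They have no stated derivation on either denominator, so the sponsor should confirm that they are intended. At 75% cleansing, under the same dilution assumptions, 1548 women would give about 65% power, so the full-trial size should be recalculated from the adherence observed.

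The cost is small. Staff already record on the operation note whether cleansing was done and with which antiseptic. At 75% the half-width of the 95% interval grows from 1.96 × √(0.75 × 0.25/250) = 5.4 points to 1.96 × √(0.75 × 0.25/125) = 7.6 points. Recruitment was open when the article was submitted, so the change needs a documented amendment to a pre-defined rule, made before adherence by arm has been seen. If that is no longer possible, cleansing-arm adherence should at least be reported beside the pooled rate and given to the oversight committee for the decision.
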